# The IBD-FITT study — moderate-intensity exercise for patients with inflammatory bowel disease with moderate disease activity: an open-label randomized controlled trial

**DOI:** 10.1186/s13063-023-07781-4

**Published:** 2023-11-20

**Keywords:** Inflammatory bowel disease, Crohn’s disease, Ulcerative colitis, Exercise

## Abstract

**Background:**

Inflammatory bowel disease (IBD), Crohn’s disease, and ulcerative colitis are chronic autoimmune lifelong diseases with fluctuating activity over time. The treatment includes medical therapy and surgery, however, there is no definite cure. Therefore, the quest for new and supplementary treatment options is imperative to improve patients’ general health and quality of life.

Physical activity and exercise have been suggested to be elements in both the prevention and supplementary treatment of IBD; however, this is based on limited underpowered trials. Thus, the role of exercise as a treatment option still has to be settled.

We aim to investigate the effect of a 12-week exercise intervention in adult patients with moderately active IBD on three categories of outcomes (1) disease-specific health-related quality of life (IBDQ); (2) general health status of the patients, i.e., waist circumference, disease activity by clinical scorings systems (Harvey Bradshaw Index, Simple Clinical Colitis Activity Index), blood pressure, blood lipids, and non-disease specific quality of life (EQ5D) scores; and (3) explorative outcomes on biomarkers (C-reactive protein and fecal calprotectin) plus different biomarkers of immunology (cytokine panel).

**Methods:**

We will apply a superiority design in this open-label randomized clinical trial including 150 patients equally allocated to intervention and usual care. The intervention will be based on a 12-week aerobic exercise program and will include two supervised exercise sessions of 60 min per week, combined with one weekly home training session. We have defined a moderate exercise level as 60–80% of patients’ maximum heart rate. The patients in the intervention group will also be offered an online video lesson of 15–25 min on lifestyle guidance, and the same online video lesson will be offered in the comparator group. Questionnaires on quality of life will be forwarded electronically both at inclusion and at the end of the study, and the patients will have blood samples, and fecal samples for calprotectin at baseline, weeks 4 and 8, as well as after 12 weeks (study end).

**Discussion:**

This will be a clinical trial investigating the effect of exercise on patients with Crohn’s disease and ulcerative colitis. This trial will add to the evidence on the possible effect of exercise and might clarify whether exercise can benefit as a supplementary treatment addendum. Thus, the trial may provide a new patient-active disease management approach.

**Trial registration:**

ClinicalTrials.gov NCT04816812. Date of first registration: March 23, 2021.

## Administrative information

Note: the numbers in curly brackets in this protocol refer to SPIRIT checklist item numbers. The order of the items has been modified to group similar items (see http://www.equator-network.org/reporting-guidelines/spirit-2013-statement-defining-standard-protocol-items-for-clinical-trials/).

## Introduction

### Background and rationale {6a}

Inflammatory bowel disease (IBD) includes Crohn’s disease and ulcerative colitis. The diseases are chronic autoimmune lifelong diseases with fluctuating disease activity over time [1, 2]. The incidences of Crohn’s disease and ulcerative colitis are increasing with approximately 60,000 patients suffering from the diseases in 2021 [1, 2]. The etiology and development of the diseases are considered to be a mixture of environmental, genetic, and behavioral factors [3, 4]. The chronic inflammation can be located in the entire gastrointestinal tract for Crohn’s disease and located in the large intestines for ulcerative colitis with common symptoms such as pain, fever, and diarrhea [3, 4].

The treatment is complex and includes medical therapy with corticosteroids, immunomodulators, biologics, and surgery, but there is no definite cure [3, 4]. Therefore, the quest for new and supplementary add-on treatment options is imperative to improve the patient’s general health and quality of life, reduce inflammation, and counteract the adverse effects of the treatment.

Lower levels of physical activity have been observed in patients with IBD compared to healthy persons [5, 6], but the role of exercise as a treatment option still has to be settled. Physical activity and exercise have been suggested to be important and safe elements in the prevention and as a supplementary option in patients with IBD, but these suggestions are only based upon limited underpowered trials [7–14]. These studies are hampered by different study populations with the inclusion of patients with different levels of disease activity at baseline, different types and intensities of physical activity plus a variety of different outcomes. However, several reviews have suggested different theoretical beneficial effects of exercise in patients with IBD [6, 15–21]. Exercise is a well-known supplementary treatment modality in other chronic diseases such as cardiovascular disease, diabetes, and rheumatoid arthritis where exercise improves general health and positively influences the quality of life. The mechanisms by which exercise could have a positive impact on patients with IBD may be linked to the direct anti-inflammatory response after moderate exercise intensities [6, 15, 16, 19, 20]. Moreover, exercise could also reduce fatty tissue in the abdomen and intestine in relation to overweight, [22] restore or increase muscle mass, positively influence the repair process of mucosal damage, increase bone health, and prevent osteoporosis [17]. Reduced muscle mass and osteopenia are well-known conditions in patients with IBD and may be related to the chronic inflammatory state/persistent inflammatory activity or malabsorption of micro and macro nutrients [17, 20, 23]. Furthermore, inactivity is especially known to be linked to heart disease and increased mortality in the general population, and to some extent, obesity and increased waist circumference are known risk factors as well [24–28].

This study will be a clinical interventional trial of the effect of exercise in patients with Crohn’s disease and ulcerative colitis. We aim to investigate the effect of exercise in adult patients with moderately active disease on three categories of outcomes (1) health-related quality of life (Inflammatory Bowel Disease Questionnaire (IBDQ)); (2) general health status of the patients such as waist circumference, disease activity by clinical scoring systems used in IBD (Harvey Bradshaw Index (HBI), Simple Clinical Colitis Activity Index (SSCAI), blood pressure, blood lipids, and non-disease specific quality of life scores (EQ5D); and (3) explorative outcomes including biomarkers of C-reactive protein and fecal calprotectin plus different biomarkers of immunology (cytokine panel). These outcomes will be examined after 12 weeks of the exercise intervention.

This study will contribute to clarify the possible effects of exercise with a properly sized clinical trial and might clarify whether exercise can benefit as a treatment addendum. The study might thus provide a new active patient disease management approach for patients with IBD.

### Objectives {7}

In adult patients with moderately active ulcerative colitis and Crohn’s disease, we want to investigate whether exercise therapy during 12 weeks including a lesson on generally healthy lifestyle is more effective compared to control patients only receiving a lesson on generally healthy lifestyle recommendations on the outcomes of interest.

### Trial design {8}

We will apply a superior trial design in this open-label randomized clinical trial with two arms, intervention, and comparison (see Fig. 1). We thus want to assess whether the intervention is better than (superiority trial) a comparator [29, 30].

**Fig. 1 Fig1:**
[figure not shown]
Study design

## Methods: participants, interventions, and outcomes

### Study setting {9}

We will recruit patients with Crohn’s disease or ulcerative colitis from specialized gastroenterology out-patient clinics located at two separate hospitals:Department of Medical Gastroenterology, Odense University Hospital, Odense, DenmarkDepartment of Medicine, Hospital of Southwest Jutland, Esbjerg, Denmark

### Eligibility criteria {10}

#### Inclusion criteria

Male or female aged between 18 and 65 years (included)Well-characterized Crohn’s disease or ulcerative colitis (physician assessment):◦ Fulfilling standard clinical, endoscopic, radiologic, and histological criteria according to clinical guidelinesA minimum of 1 year of disease duration from the time of diagnosis to the inclusionOne or more of the following pharmacological treatments within 3 months before inclusion:◦ 5-Aminosalicylic acid◦ Corticosteroids◦ Azathioprine, 6-mercaptopurine, methotrexate◦ Anti-TNFα (infliximab, adalimumab, golimumab), ustekinumab, or anti-integrin (vedolizumab)Disease activity defined by clinical disease score:◦ HBI [31] > 5 [32]◦ SCCAI [33] > 5 [32, 34]Marker for gastrointestinal inflammation:◦ Fecal calprotectin > 200 mg/g [32] or C-reactive protein ≥ 6The patient must be medically evaluated for safe participation in the intervention by the physician in charge of the patient

#### Exclusion criteria

A language barrier that prohibits the exercise instructors/supervisors to provide sufficient or safe instructions during the intervention or at the general health lessonA known heart condition that prevents patients from actively participating safely in the exercise interventionKnown pregnancy, planned pregnancy, or pregnancy during the intervention period because pregnancy needs extra precautions in the pharmacological treatment, and exercise with high intensity is not recommended limiting these patients to participate in the exercise interventionDisabling musculoskeletal injuries that limit patients from actively participating in the exercise interventionSevere disease activity manifested clinically and with the need for urgent change in medical or surgical treatment strategy evaluated by the responsible physician

The responsible physician at the respective department of gastroenterology screens through the medical records for eligible patients. The screening information is not passed on to the research project, except for the personal identifier of patients and telephone number which are passed on to the research nurse. The eligible patients are approached at their upcoming appointment with information and the possibility to participate in the trial by the physician or research nurse. This is coordinated with the research nurse to ensure only eligible patients are approached at their forthcoming appointment. At each outpatient clinic, written information and posters will be used to inform patients of the trial and create awareness for the patients on the possibility to enter the trial.

### Who will take informed consent? {26a}

We will use a consecutive inclusion of patients who fulfill the defined inclusion criteria. We plan with a recruitment period of 1–2 years. Patients will receive oral and written information on the current research project from the specialized health personnel, either physician or research nurse, in a quiet setting. After information, the patients are given at least 1 day of the consideration time, to determine whether or not they would be interested in participating and then give informed consent. If the patient wishes to have a relative present when receiving the information, this is encouraged and will be arranged at the study site. A research coordinator (nurse) will contact the patient who has accepted to be contacted after 1–3 days by telephone to confirm the acceptance of participation in the project. The patient will hereafter be asked to return a signed written pre-filled consent form.

### Additional consent provisions for collection and use of participant data and biological specimens {26b}

After obtaining written consent from the patients, the different eligibility criteria are recorded in the study’s research database (Redcap database hosted by Odense Patient Exploring Network (OPEN) situated in Denmark). This includes information on diagnosis, the onset of disease, duration of disease, disease activity by clinical scores and fecal plus blood biomarkers, and type of pharmacological treatment 3 months before inclusion. The written consent includes a permission to store blood samples and fecal samples in a research biobank also hosted by OPEN. The written consent includes a permission for the research group and regulatory authority to obtain health status from the medical record to monitor the quality and safety of the intervention.

## Interventions

### Explanation for the choice of comparators {6b}

We include patients with Crohn’s disease and ulcerative colitis with moderate disease activity as comparators and offer them one online lesson of 15–25 min on lifestyle guidance including general advice on healthy living. Specialized health personnel will present an educational video lesson. The patients in the comparison arm will receive the usual medical treatment with regular follow-up in the outpatient clinic. In this group, we will also monitor 7 days of physical activity level by accelerometry using the AX3 accelerometer [Axivity Ltd., Newcastle upon Tyne, UK] in weeks 0 and 12. The comparators have been chosen to represent the usual treatment and to help determine the efficacy of the intervention. Furthermore, all patients in the comparison arm will receive a wrist-worn heart rate monitor/fitness tracker (commercial) after completing a follow-up program identical to the patients in the intervention arm.

### Intervention description {11a}

The intervention is based on a 12-week aerobic exercise program tailored to the individual patients by physiotherapists using the principles of frequency, intensity, time, and type (FITT) aiming to increase or maintain the physical activity level to a weekly moderate level (metabolic equivalent of a task (MET) ≥ 3) [26]. This includes two supervised exercise sessions per week, each session with a length of 60 min combined with one weekly home training session. We have defined a moderate exercise level as 60–80% of their maximum heart rate, and the average intensity is calculated over the active part of the supervised session. The two weekly 60-min sessions will be supervised and the type of exercise is individually tailored by a physiotherapist to fit each patient.

The patients in the intervention arm will also be offered an online video lesson of 15–25 min on lifestyle guidance including general advice on healthy living by behavioral issues similar to the comparators. The patient will receive the usual medical treatment throughout the intervention.

The exercise intervention and home training are monitored by training diaries including frequency, intensity, time, and type of exercise. We will use the BORG 15-point scale (rate of perceived exertion) and heart rate monitors (commercial) to monitor intensity in-session [35]. We will use a heart rate monitor to quantify the cardiovascular intensity by heartbeat measure and to guide the patients during aerobic exercise to reach a moderate activity level of exercise. We use the maximum heart rate to calculate the target moderate exercise level of 60-80% and we will establish the maximum heart rate at the first supervised exercise session using a maximum cycling exercise protocol (Watt-max cycling test) or use an estimated heart rate (211–0.64*age) if the cycling can not be carried out by the participant [36, 37]. The training diary is used throughout the 12 weeks of intervention also to increase compliance/adherence and to allow proper feedback to the patients on their progress. We will also monitor the overall 7 days’ physical activity level by accelerometry using the AX3 device from the company Axivity in weeks 0 and 12.

There is solid evidence to support the appropriateness of a 12-week follow-up period when it comes to the quality of life endpoint [21, 38, 39], waist circumference [39], disease activity [21], blood pressure [21, 39], and blood lipids [21, 39]. Physical activity and exercise in patients with IBD and low to moderate disease activity have previously been found to be safe and no provoked disease activity has been observed [6, 9, 17]. The intervention will take place in-hospital at Southwest Jutland Hospital and at a private authorized physiotherapist clinic.

### Criteria for discontinuing or modifying allocated interventions {11b}

There are no specific cut-off criteria set up for discontinuing the intervention, however, if a patient experiences a significant increase in clinical disease activity or similar issues and the responsible physician estimates it as significant, the participation in the trial is discontinued.

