#### Explorative outcomes

Biomarkers:i.Fecal calprotectinii.C-reactive proteinImmunology, biomarkers (Panel - cytokines):i.Interleukin 6 ii.Interleukin 8 iii.Interleukin 10 iv.Tumor necrosis factor alpha 

The outcomes regarding the quality of life are measured at baseline and week 12, whereas the disease scores and biomarkers are measured in weeks 0, 4, 8, and 12. We will analyze blood and stool samples at baseline, 4, 8, and 12 weeks. The analyses are carried out within 5–7 days after the samples are collected, except for the analysis of cytokines which are analyzed at the end of the study.

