### Plans to promote participant retention and complete follow-up {18b}

The participating patients will be able to receive economical compensation for transportation expenses for the ambulatory visits. In case of withdrawal during follow-up in the intervention group, we will ask the patients whether they still could be interested in answering the electronic questionnaires or completing the ambulatory visits to ensure follow-up and likewise in the comparative group. However, the patients may at any time withdraw their consent to participate without any influence on their medical treatment.

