## Statistical methods

### Statistical methods for primary and secondary outcomes {20a}

We will present descriptive statistics using absolute numbers and percentages. We will use the intention-to-treat (ITT) concept in our primary analysis of the specified outcomes on between-group differences from baseline to week 12. We will use parametric or non-parametric statistics for comparing the primary outcome in the interventional arm to the comparison arm. We use a *t*-test if the data is parametric and a Wilcoxon rank-sum test if the data is non-parametric to estimate the average causal effect of the intervention. We will use mixed model analyses with random effects to evaluate repeated outcome measurements at weeks 0, 4, 8, and 12, and to account for within-patient effects on our outcome measures opting for more precise estimates of treatment effects [43]. In a supportive analysis of the data, we will use a per-protocol (PP) strategy for handling protocol non-adherence. We will report the 95% confidence intervals for the average causal effects estimates. We will report our results according to the CONSORT statement for randomized clinical trials [44]. We will use STATA to process data and calculate the estimates.

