### Methods in analysis to handle protocol non-adherence and any statistical methods to handle missing data {20c}

We will use a PP approach for handling non-adherence and examine the robustness of the ITT analysis results. In the PP analysis, we will include patients based on their adherence to the protocol considered as complete cases (e.g., patients with more than 80% show up in the intervention arm and complete follow-up in the comparison arm) and to analyze the specified outcomes on between-group differences from baseline to week 12 for this population. As specified earlier, we apply similar mixed model analyses in the PP approach as in the ITT. In supplement to the PP analyses and the possible non-adherence, we plan to use causal inference methods that include emulating data, for example, effects of different types of non-adherence or effects of concomitant treatment utilizing marginal structured models and inverted probability weighting to estimate the average treatment effect under these explorative additional questions [45, 46].

In the case of missing data in the ITT analysis, we will use multiple imputations with 10 imputations per missing value if the data is assumed to be missing at random or not missing at random. The multiple imputations will be based on regression models including predictive covariates and/or outcomes depending on which data are missing. We plan to use a linear model for continuous outcomes including covariates such as age, sex, type of disease, and disease activity. If data is assumed not to be missing at random, we will attempt to understand why and report the differences in our results by the complete-case approach and when imputation analyses are applied. To deal with any covariates or outcomes that are not normally distributed we will use log or other appropriate transformations [47]. We will perform sensitivity analysis with a best/worst approach to missing data as well as helping evaluate the robustness of the analysis.

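### Stopping for disease worsening ends trial participation rather than only the exercise, so the week-12 IBDQ can go missing for outcome-related reasons, with bias possible in either direction

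*Protocol article*

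**What the plan says.** Four parts of the protocol article bear on this.

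- **Criteria for discontinuing or modifying allocated interventions (11b).** The heading and the opening words concern the intervention: "There are no specific cut-off criteria set up for discontinuing the intervention, however, if a patient experiences a significant increase in clinical disease activity" (comparable problems count too). The consequence, however, concerns the trial: if "the responsible physician estimates it as significant, the participation in the trial is discontinued". Nothing is said about outcome data after such a stop.
- **Plans to promote participant retention (18b).** In case of withdrawal during follow-up, "we will ask the patients whether they still could be interested in answering the electronic questionnaires or completing the ambulatory visits to ensure follow-up". This applies to the comparison group as well.
- **Statistical methods (20a).** "We will use the intention-to-treat (ITT) concept in our primary analysis of the specified outcomes on between-group differences from baseline to week 12".
- **Explorative outcomes, closing paragraph.** "The outcomes regarding the quality of life are measured at baseline and week 12". The primary outcome, IBDQ, therefore has no intermediate measurement.

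The missing-data section (20c) adds multiple imputation for incomplete ITT data, whether or not the missing-at-random assumption is thought to hold. It also plans a comparison with complete cases and a best/worst sensitivity analysis.

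**The concern.** Stopping the exercise and leaving the trial are different events, and 11b merges them. The trigger is clinical disease activity, which is itself a secondary outcome (HBI and SCCAI) and plausibly moves with IBDQ. A site that applies 11b as worded would stop collecting data from the patients who are doing worst. With no IBDQ between baseline and week 12, a patient who leaves early contributes no post-baseline value of the primary outcome.

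An ITT analysis needs, as far as possible, the week-12 value of every randomised patient. A rule that makes this value missing for reasons tied to the value itself weakens the between-arm comparison that randomisation is meant to protect. The rule rests on unblinded judgement without a threshold, so it could also be applied differently in the two arms.

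**Working it through.** **1. Reading the sections together.**

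| Question | 11b | 18b | 20a |
|---|---|---|---|
| What stops? | Participation in the trial | Not stated; begins from a withdrawal | Not addressed |
| Who decides? | The responsible physician | Not stated | Not addressed |
| Are week-12 data sought? | Silent | Yes, if the patient is willing, both arms | Needed for change to week 12 |

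Section 18b may be meant to follow on from 11b, but neither refers to the other, and removal by a physician is not plainly a withdrawal. The text leaves open whether the week-12 IBDQ is requested from these patients.

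**2. Would the imputation see the worsening?** Section 20c names disease activity among its covariates. The outcomes section has disease scores at weeks 0, 4, 8 and 12. The participant timeline marks HBI and SCCAI at weeks 0 and 12 only, with C-reactive protein and calprotectin at all four visits. On the first schedule, part of the worsening would be recorded before removal. On the second, only the biomarkers would show it. Worsening between visits may be missed on either.

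**3. The plan's own figure.** Inputs from the sample size section: difference 13.8, SD 25, alpha 5% (taken as two-sided), power 80%. Normal approximation: 2 × (1.960 + 0.842)² × 25² / 13.8² = 51.5, so 52 per arm. The t-test gives 52.5, so 53 per arm, or 106 in total. This agrees with the protocol and is unaffected by the present point.

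**4. Illustration of direction and size.** From the protocol: SD of change 25 and effect 13.8. Assumed: normal changes, control mean 0, every patient with a change below a cut-off c is lost, and observed cases only are analysed. For an arm with mean μ, let a = (c − μ)/25. The fraction lost is Φ(a), and the mean of those remaining is μ + 25 × φ(a)/(1 − Φ(a)).

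Example, c = −32.04:
- Control: a = −1.28, 10.0% lost, observed mean 4.87.
- Exercise: a = (−32.04 − 13.8)/25 = −1.83, 3.3% lost, observed mean 15.72.
- Same cut-off in both arms: 15.72 − 4.87 = 10.85.
- Removal in the exercise arm only: 15.72 − 0 = 15.72.

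| Cut-off | Below cut-off, control / exercise | Same cut-off, both arms | Exercise arm only |
|---|---|---|---|
| −41.12 | 5.0% / 1.4% | 11.99 | 14.71 |
| −32.04 | 10.0% / 3.3% | 10.85 | 15.72 |
| −25 | 15.9% / 6.0% | 9.79 | 16.98 |

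If only half of the patients below the cut-off are removed, the estimates are 12.93, 12.44 and 12.06 (both arms) and 14.25, 14.74 and 15.34 (exercise arm only).

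With no true effect, a common cut-off produces no bias. Losing the worst 5% or 10% of the exercise arm only produces an apparent benefit of 2.71 or 4.87 points. In 10,000 simulated trials with 75 per arm, the two-sided rejection rate was then about 10% or 23% instead of 5%.

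**The case against.** The strongest reply is that the sections can be read in sequence: 11b stops the patient, then 18b seeks the questionnaires or visits in both arms. Surveys go electronically to the patient, so the IBDQ needs no visit. No section says that week-12 collection ceases. This stands as a possible reading and makes the fault an ambiguity rather than a proven loss of data. It does not settle the matter, because 18b does not name physician-initiated stops.

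A second reply is that 20c already plans for missing outcomes: multiple imputation with disease activity as a covariate, a complete-case comparison and best/worst bounds. Missing values handled this way do not by themselves breach ITT. That also stands in part. It would be too absolute to say that imputation cannot repair the loss, since measured disease scores and biomarkers may carry some of the reason for removal. Yet ordinary regression imputation relies on missing at random, and best/worst bounds show fragility without recovering the primary estimate.

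A reader might infer that the rule favours exercise, because those patients have two supervised sessions a week and their worsening would be noticed more often. The documents do not support that. The sessions are run by physiotherapists while the decision belongs to the responsible physician; controls have regular outpatient follow-up and samples are scheduled at weeks 4 and 8; and 11b speaks of any patient. A reader might also bring in the exclusion criterion on pregnancy during the intervention period, but that section never says such a patient leaves the ITT population.

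**Conclusion.** The point holds as a conflict of wording with a real route to bias. Taken literally, 11b makes the primary outcome missing for reasons related to it, and this fits poorly with the ITT analysis in 20a and the follow-up effort in 18b. The direction is not fixed: more frequent removal in the exercise arm may inflate the effect, while a common threshold in both arms would dilute a true benefit.

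The size cannot be derived from the documents. The 33% drop-out allowance is not broken down by reason, and no rate of worsening is given. The shifts of roughly −4 to +3 points around 13.8 (9.79 − 13.8 = −4.01; 16.98 − 13.8 = +3.18) depend on the assumed cut-offs and on an observed-case analysis, which is not the planned imputed one. They show that the effect could matter, not what it will be. When exercise should be stopped is a clinical matter and is not judged here.

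**What to change.** Reconcile 11b, 18b and 20a and leave the clinical decision with the physician. State that a patient stopped for worsening, in either arm:

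- is still asked for the week-12 IBDQ and visit unless consent is withdrawn;
- is analysed in the arm to which they were randomised;
- has the reason and date recorded, with these stops reported by arm.

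The cost is a change of wording and a few extra follow-up contacts.

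The trial status section extends inclusion to 1 May 2023. Twelve weeks later is late July 2023, before the article's publication on 20 November 2023, so follow-up may already be complete. In that case the missing scores may not be recoverable. What remains is to keep all randomised patients in the ITT analysis and to report the number of these discontinuations by arm, so that readers can judge the imputed and best/worst results against them.
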